**Methods:**

A prospective, quantitative, experimental control study will be carried out in Reiyukai Eiko Masunaga Eye Hospital, located in Banepa, Kavrepalanchok, Nepal. All patients undergoing cataract surgery meeting the inclusion and exclusion criteria irrespective of the type of surgery (small-incision cataract surgery or phacoemulsification) will be included in the study. The patients will be randomly assigned to 1 of 2 groups. Patients in group 1 will be examined on day 1, day 7, and day 30, whereas patients in group 2 will be examined on day 1 and once between days 25 to 30. The minimum clinically important difference (MCID) in our study will be set according to the improvement in the Snellen visual acuity chart.

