**Conclusions:**

We aim to conclude that we can safely defer the 1-week postoperative follow-up visit in patients undergoing uncomplicated cataract surgery and that, moreover, we can reduce the patient load at the hospital and decrease patient expenses by decreasing the frequency of hospital visits.

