### Specific Objectives

The specific objectives are (1) to compare postoperative visual outcomes after a day 0 examination in patients with either 2 follow‑up visits, one on day 7 and the other on day 30, or 1 ophthalmic follow‑up visit between day 25 and day 30; (2) to assess the safety of deferring the first follow‑up visit at 1 week; and (3) to perform a cost-benefit analysis of the intervention.

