## Results

More than 526 participants will be enrolled in the study, with a minimum of 263 assigned to the intervention group (deferred follow-up visits) and a minimum of 263 to the comparison group (standard practice of early postoperative follow-up visits). The sample will have diverse demographics, ensuring a representative population.

Visual acuity measurements will be obtained for both groups during the follow-up period. We will be able to statistically compute whether the deferred follow-up visit group demonstrates comparable visual acuity outcomes to the comparison group. This will be inferred if there are no statistically significant differences between the two groups in terms of visual acuity outcomes (*P*>.05).

Among the participants in the deferred follow-up visit group, the number of patients who experience postoperative complications during the 4-week follow-up period will be compared with the group with the 1-week follow up visit.

We will also determine if participants in the deferred follow-up visit group report high levels of satisfaction with the extended recovery period and reduced travel burden. The number of participants who express that deferring follow-up visits provided them with convenience and comfort during the recovery phase will be mentioned.

We will determine if reduction in early postoperative visits allows health care providers to allocate their time and expertise more efficiently, focusing on patients with immediate needs or complex postoperative care requirements.

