## Discussion

### Expected Findings

The proposed study will investigate the feasibility and potential benefits of deferring postoperative follow-up visits up to 4 weeks after uneventful cataract surgery in a tertiary level eye hospital in Kavrepalanchok.

Deferring postoperative follow-up visits will allow patients to recover in the familiar environment of their homes, reducing the need for immediate travel and associated costs. This can have a positive impact on patient satisfaction and comfort during the recovery period. By avoiding unnecessary trips to the hospital, patients may experience reduced anxiety and stress, leading to an improved overall experience.

By spacing out follow-up visits, health care providers can optimize resource allocation within the tertiary level eye hospital. This approach will allow health care personnel to allocate their time and expertise more efficiently, focusing on patients who require immediate attention or complex postoperative care. Moreover, it can potentially reduce the burden on health care facilities, as fewer appointments are scheduled during the early postoperative period.

Deferring follow-up visits may also improve access to care, particularly for patients residing in remote areas. Traveling to health care facilities shortly after surgery can be challenging, especially for individuals with limited mobility or limited access to transportation. By extending the follow-up period, patients from distant locations can receive necessary care without the immediate need for travel, increasing the likelihood of their adherence to follow-up appointments.

One major concern related to deferring follow-up visits is the potential delay in detecting postoperative complications. Early postoperative visits allow health care providers to closely monitor patients for any signs of infection, inflammation, or other adverse events. When extending the follow-up period, it is crucial to educate patients regarding the signs and symptoms of postoperative complications so that they can visit the hospital, if required, on time. Patients should receive comprehensive information about self-care, potential warning signs, and instructions on when to seek medical attention. This will empower patients to actively participate in their own recovery and promote a sense of responsibility for their eye health.

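### The 4-week complication comparison counts day-7 findings that only group 1 is scheduled to have looked for, so with equal true risk it is expected to favour deferral

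*Protocol article*

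**What the plan says.** Whether the 1-week visit can be dropped without harm is the second specific objective of the protocol article, which begins: "to assess the safety of deferring the first". The abstract gives the intended conclusion: "We aim to conclude that we can safely defer" that visit.

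The Results section states how complications will be handled: "the number of patients who experience postoperative complications during the 4-week follow-up period will be compared" between the two groups. Complications are not listed under Primary Outcome or Secondary Outcome.

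The observation schedules differ by design. The abstract's Methods give the standard arm three examinations: "Patients in group 1 will be examined on day 1, day 7, and day 30". The deferred arm has only two, with nothing scheduled in the first weeks after discharge: "patients in group 2 will be examined on day 1 and once between days 25 to 30". Under Study Design, Setting, and Participants, slit lamp biomicroscopy by a blinded ophthalmologist belongs to each follow-up visit, and patients are taught which signs and symptoms to watch for.

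The Discussion (Expected Findings) recognises the risk: "One major concern related to deferring follow-up visits is the potential delay in detecting postoperative complications". The article does not restrict the comparison to the common final examination, set apart what is found at day 7, or say that unscheduled visits feed the complication data in the same way in both groups.

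**The concern.** A cumulative 4-week count depends on how often someone looks. Group 1 is examined once more than group 2, at a time when early postoperative findings may be present. The missing examination is the intervention itself, so the two groups differ in ascertainment because of the randomised treatment. Masking the examiners cannot correct this, because in group 2 there is no day-7 examination to mask.

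The expected direction matches the conclusion that the study hopes to reach. An event that goes unseen lowers the count under deferral, so the harm that the article itself raises, late detection, can register as a lower complication rate. Objective 2 could then be answered with reassurance that reflects fewer examinations and not fewer complications.

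**Working it through.** **Plan's own figure.** The article states no complication rate, complication margin or sample size for complications, so there is nothing to reproduce on this point. The 263 per group in Sample Size and Sampling Technique is derived from visual acuity inputs. It is used below only as the number of patients per group.

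**Schedules side by side.**

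| | Day 1 | Day 7 | Final visit |
|---|---|---|---|
| Group 1 | examined | examined | day 30 |
| Group 2 | examined | only if the patient returns unprompted | once in days 25 to 30 |

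**Detection model (assumptions, not document figures).**
- p is the true 4-week risk, equal in both groups.
- t is the share of complications visible only around day 7. The range taken is 25 to 75%.
- u is the share of those that present at an unscheduled visit in group 2. The range taken is 0 to 50%.
- Group 1 is taken to detect all events.

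Observed risk in group 1 = p. Observed risk in group 2 = p × [1 − t(1 − u)]. The apparent risk ratio (deferred/standard) is therefore 1 − t(1 − u), whatever p is.

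- Mildest corner: t = 0.25, u = 0.5 gives 1 − 0.125 = 0.875, about 0.88.
- Strongest corner: t = 0.75, u = 0 gives 1 − 0.75 = 0.25.

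**Expected counts at an assumed p of 5%, t = 0.5.** Group 1: 263 × 0.05 = 13.2.
- u = 0: group 2 shows 13.15 × 0.5 = 6.6. Rounded, 13 versus 7, Fisher P about .25.
- u = 0.5: group 2 shows 13.15 × 0.75 = 9.9. Rounded, 13 versus 10, Fisher P about .67.

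**A harsher case, and its sensitivity.** Suppose only 30% of events are still visible at the final visit (t = 0.7).

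| Assumed true risk | No unscheduled returns | Half of the otherwise missed events present |
|---|---|---|
| 8% | 21 vs 6, P about .005 | 21 vs 14, P about .29 |
| 5% | 13 vs 4, P about .045 | 13 vs 9, P about .51 |

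**Masking of a true harm.** If deferral doubled the true risk, the apparent ratio would be 2 × [1 − t(1 − u)]. With t = 0.5 and u = 0 this is 2 × 0.5 = 1.0, that is, no visible difference.

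**What 263 per group can say about safety.** With zero events in 263, the upper limit is 1 − 0.05^(1/263) = 1.13% (one-sided 95%) or 1 − 0.025^(1/263) = 1.39% (two-sided 95%). At an assumed 2% risk in each group, the half-width of the 95% CI for the difference is 1.96 × √(2 × 0.02 × 0.98/263) = 0.024, or 2.4 percentage points.

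**The case against.** **Patients are told to come back.** The article provides for education on warning signs, and the Discussion expects patients to return when needed. A model with no unscheduled returns is therefore a corner case. This stands. A reader might infer from the harsher case that the trial will show significantly fewer complications under deferral. The documents do not support that: the significant results need 70% of events to vanish by the final visit and nobody to return early. Once half of the otherwise missed events present, significance is gone. A large true harm could also outweigh the bias. The direction is expected, not certain.

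**Resolved events matter least, and vision is measured alike.** Complications that clear without sequelae are the least consequential. Lasting damage can be seen in both groups at about 1 month, when a blinded optometrist also tests acuity. This stands too, and it is a reason to base the comparison on that visit. It does not rescue a count that mixes in day-7 findings.

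**Counts, intervals and power.** With equal groups, counts and proportions carry the same information, so comparing numbers is a minor matter. A missing confidence limit, taken alone, is detail that a condensed article may leave to a fuller document. A reader might also infer that the trial is underpowered for its safety objective. The article claims no power for complications and states no margin, and the answer depends on the margin: with one-sided 0.025 and 80% power, a 2-point margin at a 2% rate needs 770 per group, a 5-point margin only 124. What remains is that the wording of the safety conclusion should not go beyond what the interval allows.

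**Conclusion.** The concern holds in this form: the stated between-group comparison of complications is subject to unequal ascertainment built into the design, and with equal true risk it is expected to favour deferral. It bears on specific objective 2 and on the conclusion announced in the abstract. Under the assumed ranges the apparent risk ratio lies between about 0.88 and 0.25. No rate, transient share or return rate comes from the documents, so these figures show plausible size and are not a forecast. The defect lies in the comparison that the article states, so it does not turn on what an unseen analysis plan might add. Separately, even zero events in 263 patients would exclude only risks above about 1.1% (one-sided 95%) or 1.4% (two-sided), so an unqualified statement of safety would go further than the data can.

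**What to change.** 1. Define the between-group safety outcome as complications or sequelae present at the common 1-month examination, plus those diagnosed at unscheduled, symptom-driven visits, recorded on the same form and in the same way in both groups.
2. Report findings seen only at the scheduled day-7 visit separately and descriptively, for group 1 alone.
3. Give the risk difference with its 95% CI.
4. Word the conclusion on safe deferral to that interval, including the upper limit that remains compatible with the data.

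Show the two components of the outcome separately as well as combined. The unscheduled part is not perfectly symmetrical, because a problem found at day 7 in group 1 may forestall an unscheduled visit there.

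The cost is a change of outcome wording, a field for type of visit on the data form and a split table. No visit changes. The downside is fewer events in the formal comparison and a more modest safety claim.

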## Methods

### Study Design, Setting, and Participants

This will be a prospective, quantitative, experimental, noninferiority control study of health services use. Selected patients undergoing cataract surgery at Reiyukai Eiko Masunaga Eye Hospital irrespective of the type of surgery (SICS or phacoemulsification) will be included in the study.

All enrolled patients will undergo an examination on the first postoperative day conducted by an ophthalmologist who is unaware of the patient’s group assignment. Subsequently, the patient will proceed to the counselor’s office, where a unique identification number will be generated and the patient will be randomized into either group 1 or group 2.

In group 1, patients will be instructed to attend follow-up visits at 1 week and 1 month postoperatively. In group 2, patients will be instructed to attend a follow-up visit at 1 month postoperatively only. During the visit, the patients will receive detailed guidance on the appropriate use of medications and be educated about the signs and symptoms they should be vigilant for. The specific date of the postoperative visit will also be communicated.

At each follow-up visit, the patient will directly visit the counselor’s office. Upon arrival, they will be provided with a blank sheet of paper containing the unique identification number assigned to them on the first postoperative day. Visual acuity testing will be conducted by a blinded optometrist, while slit lamp biomicroscopy will be performed by a blinded ophthalmologist. Before leaving the hospital, the patient will return the paper to the counselor, who will then enter the necessary information into the patient’s file. 

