### Expected Outcome of the Research Results

We expect to determine whether we can defer the 1-week cataract surgery follow-up visit of patients to the hospital.

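### The only stated safety comparison is a 4-week complication count by arm, which cannot show whether the day 7 visit detected a problem or changed care

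*Protocol article*

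**What the plan says.** The question is put plainly in the Expected Outcome section: "We expect to determine whether we can defer the 1-week cataract surgery follow-up visit". The second item under Specific Objectives is "to assess the safety of deferring the first follow‑up visit at 1 week", and the abstract's Conclusions paragraph hopes to call deferral safe. The Discussion (Expected Findings) names the hazard: "One major concern related to deferring follow-up visits is the potential delay in detecting postoperative complications". It relies on patient education so that people with warning signs come back by themselves.

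The arms differ in how often anyone looks. According to the abstract's Methods, "Patients in group 1 will be examined on day 1, day 7, and day 30", while "patients in group 2 will be examined on day 1 and once between days 25 to 30". The Study Design section gives the content of each follow-up visit: "Visual acuity testing will be conducted by a blinded optometrist, while slit lamp biomicroscopy will be performed by a blinded ophthalmologist".

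The Results section states one complication analysis, in which for deferred patients "the number of patients who experience postoperative complications during the 4-week follow-up period will be compared with the group with the 1-week follow up visit". The article describes no analysis of what the day 7 examination found or what followed from it. Payments for medicine and investigations are collected visit by visit, but only for costing (Secondary Outcome).

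**The concern.** The intervention is the removal of one visit. Its possible harm is that a problem the visit would have caught is caught later or not at all. A cumulative count of patients with any complication has no time element, does not record how the problem was detected, and does not record whether management changed. Two trials with the same counts could have very different day 7 visits: in one the visit finds nothing, in the other it regularly finds silent problems that are then treated.

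The count can also err in the unsafe direction. An early problem that causes no symptoms and resolves before days 25 to 30 can be counted only in the arm that was examined on day 7. Less looking then lowers the deferred arm's count and makes deferral look safer.

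The count is also imprecise at low event rates. A null result is likely even if rates differ materially, and it could be taken as reassurance about a visit whose contribution was never examined.

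**Working it through.** **Inputs.** At least 263 patients per group (Sample Size; Results). Group 1 has scheduled follow-up on day 7 and day 30; group 2 has one visit on days 25 to 30 (abstract, Methods). The article gives no complication rate, so every rate below is an assumption.

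The figure 263 was derived for visual acuity. The printed formula gives 2 × (1.96 + 1.645)² × (0.1125/0.025)² = 526.3 per group; 263.2 results only without the leading 2. That is a separate matter. Here 263 serves only as the stated number of patients per arm.

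**1. Precision of the planned count.** For a common rate p in both arms, the 95% half-width of the difference is 1.96 × √(2p(1 − p)/263).

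- p = 0.02: 1.96 × √(0.0392/263) = 0.024, or 2.4 points.
- p = 0.05: 1.96 × √(0.095/263) = 0.037, or 3.7 points.

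**2. Power of the planned count.** Normal approximation, two-sided 0.05, 263 per arm:

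| Assumed rates | Power |
|---|---|
| 1% vs 2% | 15% |
| 2% vs 4% | 27% |
| 5% vs 8% | 29% |
| 5% vs 10% | 59% |

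**3. Effect of unequal looking.** Assume the same true incidence in both arms: 5% early problems and 2% late ones. Suppose group 1 detects all of them, and 30% of the early ones still come to light in group 2.

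- Group 1: 263 × (0.05 + 0.02) = 18.4 patients.
- Group 2: 263 × (0.05 × 0.30 + 0.02) = 9.2 patients.

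If 60% come to light, group 2 has 263 × (0.05 × 0.60 + 0.02) = 13.2. If all do, the arms are equal. The deferred arm's count falls with detection alone.

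**4. What the day 7 visits could show.** Exact (Clopper-Pearson) 95% limits for x visits with a care-changing finding out of 263 attended. For x = 0 the upper limit is 1 − 0.025^(1/263) = 1.39%.

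| x | Proportion | 95% CI |
|---|---|---|
| 0 | 0% | 0 to 1.4% |
| 5 | 1.9% | 0.6 to 4.4% |
| 13 | 4.9% | 2.7 to 8.3% |

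A finding with a true rate of 1% would appear at least once with probability 1 − 0.99²⁶³ = 0.93.

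**5. What that proportion means.** A symptomatic patient may return unprompted, so the asymptomatic part is the relevant one. Some of those findings would resolve, and some would still be seen on days 25 to 30. The asymptomatic yield therefore tends to overstate what deferral loses. The bound is approximate because some symptomatic patients may not return; unscheduled visits in both groups bear on that.

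**The case against.** The strongest reply is that this asks for an additional analysis and does not correct an error. A condensed article need not list every table, and a complications-by-visit table may sit in an analysis plan that is not shown. That stands in part: it cannot be said that the trial will never estimate the day 7 yield. But the article does fix a measure for its safety objective, and that measure does not fit the hazard the article names.

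A second reply is that safety is comparative, whereas the yield has no comparator and measures process: a changed treatment is not a prevented harm. This is right, and is why the yield should accompany the two-arm count, not replace it. Nor should much be made of its narrower interval. At 5%, a single proportion has a half-width of 1.96 × √(0.0475/263) = 2.6 points against 3.7 for the difference. That is the usual √2 ratio, and the two quantities differ.

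A reader might infer that day 7 findings directly show what dropping the visit would miss, and that their asymptomatic part is the proportion lost. The documents do not support this, because group 2 is examined on days 25 to 30 and some findings would resolve or be seen then. A reader might also infer that the day 7 data have no other use. In fact acuity over the 4 weeks belongs to the primary outcome, and per-visit payments feed the costing.

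Two further limits stand. The exclusion criteria remove patients who miss follow-up visits, so the yield describes attenders only. And although examiners are described as blinded, only group 1 has a scheduled 1-week visit, so timing may reveal the group.

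**Conclusion.** The concern holds in a limited form. The one complication analysis the article states for its safety objective cannot address delayed detection, and it confounds occurrence with detection because scheduled follow-up examinations are two against one. Under the assumed rates, the two-arm difference is known only to within 2.4 to 3.7 points. With 30% of early problems coming to light in group 2, equal true incidence could give about 18 against 9 counted patients.

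Visits already planned can supply a useful complement: with 263 attended day 7 visits, zero care-changing findings would exclude a yield above 1.4%. This rests on all 263 attending and on a consistent judgement of what counts as a change in care. It is supporting evidence and not a decision rule, since the documents give no acceptable limit for such a yield. The change should be made, but the two-arm comparison remains necessary.

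**What to change.** Keep the two-arm count and add a named safety analysis:

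- In group 1, report the proportion of attended day 7 visits with a finding that changed treatment or follow-up, with an exact 95% interval, and state how many scheduled day 7 visits were not attended.
- Split it by whether the patient reported, before the examination, one of the warning symptoms taught on the first postoperative day.
- Report unscheduled visits in both groups.
- Describe the asymptomatic part as an approximate upper bound, among attenders, on what deferral could miss, and present it beside any statement that deferral is safe.
- State that the 4-week count reflects detection as well as occurrence.

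The cost is two tick-box fields on the day 7 sheet, a record of unscheduled visits in both arms, and one proportion with its interval. No scheduled visit or procedure is added. The weakness is that a change in treatment or follow-up rests on the judgement of an examiner who may infer the group from the visit date; recording the symptom answer before the examination protects at least the split.

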### Exclusion Criteria

Patients will be excluded if (1) there are complications during the surgery that warrant more frequent follow-up visits (eg, premature entry, posterior capsular rupture, zonular dialysis, postoperative hyphema, toxic anterior segment syndrome, or postoperative fibrin in the anterior chamber); (2) the surgery is for complicated cataract, traumatic cataract, ocular hypertension, or if the patient has drug allergies; (3) the patients has a history of diseases that might affect postoperative visual outcomes, such as uveitis, glaucoma, viral keratitis, corneal scarring, hypertensive retinopathy, diabetic retinopathy, central retinal vein occlusion, branched retinal vein occlusion, or age-related macular degeneration; (4) the patient is unwilling to participate or does not provide written consent; and (5) the patient misses the follow-up visits.

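### The 4-week complication count compares arms with unequal scheduled examinations and ignores status at the final visit, so it can read equal or favour deferral while more deferred patients still have a complication

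*Protocol article*

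**What the plan says.** The safety of deferral is a specific objective of the protocol article: "to assess the safety of deferring the first follow‑up visit at 1 week". The Conclusions of the Abstract aim to state that the 1-week visit can be deferred safely. The only complication comparison between the groups is in the Results section and starts from the deferred arm: "the number of patients who experience postoperative complications during the 4-week follow-up period will be compared with the group with the 1-week follow up visit".

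The schedule is in Study Design, Setting, and Participants. The control arm has two visits after discharge: "In group 1, patients will be instructed to attend follow-up visits at 1 week and 1 month postoperatively". The deferred arm loses the first of them: "In group 2, patients will be instructed to attend a follow-up visit at 1 month postoperatively only". The Abstract places the single group 2 visit between days 25 and 30. At each follow-up visit, "Visual acuity testing will be conducted by a blinded optometrist, while slit lamp biomicroscopy will be performed by a blinded ophthalmologist". Patients are also to "be educated about the signs and symptoms they should be vigilant for", so unscheduled returns are possible, but no return rate is given.

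Under Expected Findings the authors write: "One major concern related to deferring follow-up visits is the potential delay in detecting postoperative complications". Criterion 5 of the Exclusion Criteria removes a participant if "the patient misses the follow-up visits".

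**The concern.** The intervention removes one of the two scheduled occasions on which a complication can be seen. A cumulative count of patients depends directly on the number of such occasions, and it uses neither the time of detection nor the state of the eye at the end. For complications that arise in the first week and do not bring the patient back early, two things follow.

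1. If they persist, both arms count them and the comparison shows no difference, although group 2 cases are found 25 − 7 = 18 to 30 − 7 = 23 days later.
2. If some resolve before days 25 to 30, those can be counted in group 1 only, and the comparison favours deferral.

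In both cases more group 2 patients may still have a complication at the final visit, because group 1 cases were treated from day 7. The harm that the article itself names is then invisible to, or reversed by, the measure meant to detect it. An analysis plan that followed the Results section would inherit this.

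Criterion 5 adds a second imbalance. If one missed visit is enough to exclude, group 1 has two chances of exclusion and group 2 has one, so the day-7 visit also affects who is counted.

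**Working it through.** **Inputs.** The documents supply n = 263 per arm (Sample Size and Sampling Technique; Results) and the visit days. The figure of 263 was derived for visual acuity and serves here only as the arm size. (The printed formula in fact evaluates to 526.3, or 263.2 without its leading factor 2; that is a separate matter.) There is no complication rate, margin or power to reproduce. The following are assumptions:

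- p: first-week complication rate, the same in both arms
- q: share still present at the final visit if untreated
- c: share of those cleared by treatment started at day 7 or at an early return
- r: share of group 2 cases that return early

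Detection at each examination is taken as complete.

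**Formulas.**

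- 4-week count: group 1 = np; group 2 = np(r + (1 − r)q). Group 1 minus group 2 = np(1 − r)(1 − q), which is never negative.
- Present at final visit: group 1 = npq(1 − c); group 2 = npq(r(1 − c) + (1 − r)). Group 2 minus group 1 = npqc(1 − r), which is positive whenever treatment helps (c > 0), something persists (q > 0) and not everyone returns early (r < 1).

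Under equal true incidence the two measures therefore never point the same way. The count is neutral or favours deferral; final status is neutral or goes against it.

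**Base case.** With p = 0.05, q = 0.7, c = 0.8 and r = 0, np = 263 × 0.05 = 13.15. Group 2 count = 13.15 × 0.7 = 9.2. Final status is 13.15 × 0.7 × 0.2 = 1.8 in group 1 and 13.15 × 0.7 = 9.2 in group 2.

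**Range.** Pairs are group 1 against group 2. Differences are group 2 minus group 1 in percentage points, with Newcombe 95% intervals on the rounded final-visit counts out of 263.

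| p | q | c | r | Count | Final visit | Rounded | Difference (95% CI) |
|---|---|---|---|---|---|---|---|
| 5% | 0.7 | 0.8 | 0 | 13.2 v 9.2 | 1.8 v 9.2 | 2 v 9 | 2.7 (0.1 to 5.7) |
| 5% | 0.7 | 0.8 | 0.5 | 13.2 v 11.2 | 1.8 v 5.5 | 2 v 6 | 1.5 (−0.8 to 4.2) |
| 5% | 0.7 | 0.8 | 0.9 | 13.2 v 12.8 | 1.8 v 2.6 | 2 v 3 | 0.4 (−1.7 to 2.6) |
| 5% | 0.7 | 0.5 | 0 | 13.2 v 9.2 | 4.6 v 9.2 | 5 v 9 | 1.5 (−1.4 to 4.7) |
| 2% | 0.7 | 0.8 | 0 | 5.3 v 3.7 | 0.7 v 3.7 | 1 v 4 | 1.1 (−0.8 to 3.5) |
| 10% | 0.7 | 0.8 | 0 | 26.3 v 18.4 | 3.7 v 18.4 | 4 v 18 | 5.3 (1.9 to 9.2) |
| 5% | 1.0 | 0.8 | 0 | 13.2 v 13.2 | 2.6 v 13.2 | 3 v 13 | 3.8 (0.8 to 7.2) |

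The last row is case 1 (equal counts); the others are case 2.

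**Imperfect detection.** A wider model let day-7 detection fall to 50%, final-visit detection to 80%, and early return vary from 0 to 75%. In all 1,440 parameter sets in which treated cases resolved more often than unseen ones, the group 1 count was at least the group 2 count and group 2 had more complications at the final visit. Where treatment added nothing, final status was equal.

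**Criterion 5.** If one missed visit excludes and visits are missed independently with probability m, group 1 keeps 263(1 − m)² and group 2 keeps 263(1 − m). For m = 5%, 10% and 20% this leaves 237 v 250, 213 v 237 and 168 v 210.

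**The case against.** The sentence in Results is a short statement in a condensed article. Definitions, dating and visit-level tables may stand in a fuller document, a 4-week incidence count is a standard measure, and nothing bars reporting slit-lamp findings by visit. That is fair as far as it goes. However, the article does fix a measure, and that measure is poorly matched to the stated objective; this is more than a missing detail.

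The size is open to stronger challenge, and most of that challenge stands:

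- Patients are taught warning signs, so no early return is the extreme case.
- Enrolment is restricted to low-risk eyes already examined on day 1, so 5% may be high.
- Unseen group 2 patients still use their prescribed medication, and the 80% clearance has no source in the article.
- The base-case 9 v 2 is borderline (Fisher's exact p = 0.063).
- Complications that start after day 7 dilute the contrast. Adding an assumed 5 per arm gives 14 v 7, an interval of −0.8 to 6.3 points.

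These points reduce or blur the effect; none reverses its direction.

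Visual acuity, the primary outcome, is measured in both arms at month 1 by a blinded optometrist and captures part of the harm. Safety is nevertheless listed as an objective separate from visual outcomes. Finally, the criterion 5 point depends on reading the plural as any single missed visit, and it reaches the acuity analysis too.

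**Conclusion.** The concern holds within its limits. For first-week complications that prompt no early return, the planned count can only read equal or favour deferral, and it cannot show delay. The direction rests on one clinical assumption: that a complication found and treated at day 7 is more likely to have cleared by the final visit than one not seen. The article's own worry about delayed detection implies this but does not quantify it.

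The size rests wholly on assumed rates. With no early return, the excess of group 2 patients with a complication at the final visit runs from 3 of 263 (2% rate) to 14 of 263 (10% rate) on rounded counts. It is clear of zero only when few affected patients return early and treatment is effective, and it is under one patient at 90% early return. The point does not cover complications that bring the patient back or that begin after day 7. The change should be made, but the primary acuity comparison does not depend on it.

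**What to change.** Keep the 4-week count and add to Results, as a co-equal safety comparison: *the number of patients with a postoperative complication present at the final blinded slit-lamp examination (day 30 in group 1, days 25 to 30 in group 2), by randomised group, with a 95% confidence interval for the difference.* Final status alone would miss complications that were treated and cleared, so it belongs beside the count and does not replace it. Base any statement that deferral is safe on both. Limit criterion 5 so that missing only the day-7 visit does not exclude a group 1 patient from either comparison. Report time from surgery to first detection, split by scheduled and unscheduled visits, as description only, because the visit schedule largely sets it.

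The cost is one or two sentences of analysis text, the limit on criterion 5, and a few fields in the proforma, which Data Collection Technique and Tools says is still to be developed: a list of what counts as a complication, status at the final visit, date found and visit type. No new examination is needed.

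There are two downsides. Few events give wide intervals (13 v 13 of 263 gives −3.9 to 3.9 points), so the safety statement may have to be more cautious. Group 2 may also be examined up to 5 days earlier than group 1, which slightly disfavours deferral.
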